## Abstract

**Background:**

People living with HIV often struggle with mental health comorbidities that lower their antiretroviral therapy (ART) adherence. There is growing evidence that depression treatment may improve ART adherence and result in improved HIV outcomes. Given that mental health services are severely underequipped in low-resource settings, including in Uganda, new solutions to increase access to mental health care and close the treatment gap are urgently needed. This protocol paper presents the Suubi-Mhealth study, which proposed to develop a mobile health (mHealth) intervention for use among Ugandan youths (14-17 years) with comorbid HIV and depression, taking into account their unique contextual, cultural, and developmental needs.

**Objective:**

The proposed study is guided by the following objectives: (1) to develop and iteratively refine an intervention protocol for Suubi-Mhealth based on formative work to understand the needs of youths living with HIV; (2) to explore the feasibility and acceptability of Suubi-Mhealth on a small scale to inform subsequent refinement; (3) to test the preliminary impact of Suubi-Mhealth versus a waitlist control group on youths’ outcomes, including depression and treatment adherence; and (4) to examine barriers and facilitators for integrating Suubi-Mhealth into health care settings.

**Methods:**

Youths will be eligible to participate in the study if they are (1) 14-17 years of age, (2) HIV-positive and aware of their status, (3) receiving care and ART from one of the participating clinics, and (4) living within a family. The study will be conducted in 2 phases. In phase 1, we will conduct focus group discussions with youths and health care providers, for feedback on the proposed intervention content and methods, and explore the feasibility and acceptability of the intervention. In phase II, we will pilot-test the preliminary impact of the intervention on reducing depression and improving ART adherence. Assessments will be conducted at baseline, 1-, 2-, and 6-months post intervention completion.

**Results:**

Participant recruitment for phase 1 is completed. Youths and health care providers participated in focus group discussions to share their feedback on the proposed Suubi-Mhealth intervention content, methods, design, and format. Transcription and translation of focus group discussions have been completed. The team is currently developing Suubi-Mhealth content based on participants’ feedback.

**Conclusions:**

This study will lay important groundwork for several initiatives at the intersection of digital therapeutics, HIV treatment, and mental health, especially among sub-Saharan African youths, as they transition through adolescence and into adult HIV care settings.

**Trial Registration:**

ClinicalTrials.gov NCT05965245; https://clinicaltrials.gov/study/NCT05965245

**International Registered Report Identifier (IRRID):**

DERR1-10.2196/54635

## Introduction

### Overview

Globally, an estimated 39 million people were living with HIV in 2022; of these, 1.5 million were children <15 years [1]. Approximately 84% of new HIV infections among children <15 years occurred in sub-Saharan Africa (SSA) [1]. HIV disproportionately impacts children from poor and disadvantaged backgrounds, and the prevalence of HIV–related complications and mortality are highest among those struggling with poverty and deprivation [2,3]. Poor children living with HIV are more likely to experience compromised health, inconsistent antiretroviral therapy (ART) adherence, and elevated mental health difficulties, including depression, which increases the risk of HIV transmission [2,3]. In Uganda, the focus of this study and one of the SSA countries hardest hit by HIV, over 80,000 children (0-14 years) are living with HIV [4]. Improvements in access and use of HIV services, including testing, care, and availability of free ART have reduced child mortality [5] and resulted in an increased number of children now growing up with a highly stigmatizing and transmittable infection.

Depression is the most common psychiatric disorder among people living with HIV [6,7]. The prevalence of depression among people living with HIV is estimated to be as high as 63% in SSA [8]. Among young people, the prevalence of major depression is estimated between 16% and 40.8% [9]. Depression is associated with compounding and exacerbating negative HIV outcomes [10,11]. While high levels of ART adherence are necessary for young people to benefit individually from ART, as well as for reducing the risk of HIV transmission, depression has been found to significantly impede ART adherence [10,11]. Previous studies have found that patients with depression are nearly 3 times more likely to be nonadherent to medication regimens than patients without depression [12,13]. Depression can impact ART adherence through isolation from social support, impaired adaptive coping skills, apathy, forgetfulness, and hopelessness [14]. In addition, depression-related fatigue, low energy, inconsistent or lack of sleep, and loss of appetite may make it hard to take ART and attend medical appointments [15]. Indeed, due to limited ART adherence and associated medical complications, patients with depression have a higher risk of increased HIV viral load [16], rapid disease progression, and mortality relative to patients who are not depressed [17,18], making this a crucial population with which to intervene. Thus, failure to address the mental health needs of youths living with HIV, including depression, may lead to costly long-term consequences.

There is growing evidence that depression treatment may improve ART adherence and result in improved HIV outcomes [19,20]. Studies have shown that treating depression was associated with up to 83% higher odds of adhering to HIV treatment [19,21]. Among adults, improvements in cognitive processes have been shown to increase confidence and motivation to engage in HIV management behaviors [22,23]. However, few studies targeting the treatment of depression and evaluating the subsequent improvement in ART adherence have been conducted with adolescents [24], and even fewer studies have been conducted with populations from SSA [25]. Therefore, it is crucial to develop interventions for depression that are tailored to the needs of this specific population, given the prevalence of HIV in the region and the elevated risk factors and myriad barriers to care.

Youths are the lowest ART adherent age group and are at the highest risk of dropping out of ART care programs [26-28]. Poor ART adherence among youths is due, in part, to their transition from youth-focused care into adult-focused care that is less accommodating to the needs of this age group who are at the cusp of taking on new roles and responsibilities including their own disease management [29-31]. Moreover, insufficient staff training to support youths living with HIV during this period, lack of pediatric ART formulations in adult clinics, insufficient clinical monitoring, rigid scheduling that interferes with schooling, as well as loss of pediatric clinic relations with peers and clinical support staff all contribute to poor engagement in care during this transition period [27,28]. Indeed, studies indicate that this period in the life course is associated with a significant drop in ART adherence with up to 50% of youths discontinuing their HIV care entirely during this shift [32]. Thus, targeted interventions to improve retention and treatment outcomes during this period are critical.

Cognitive behavioral therapy (CBT) is a promising approach to reduce depression and improve ART adherence [33-35]. CBT is a form of psychotherapy that is focused on changing patterns of thinking and the associated behaviors [36]. CBT has a growing evidence base as an efficacious approach to reducing depressive symptoms and improving ART adherence among people living with HIV [24,33,37-39]. Moreover, evidence supports the efficacy and effectiveness of CBT in reducing self-stigma for people with mental illness—one of the major barriers to treatment adherence [40,41]. Some key principles of CBT that specifically target ART adherence and depression include instruction for behavioral activation, cognitive restructuring that addresses negative automatic thoughts, problem-solving, and relaxation training [39,42,43]. Despite the promise of CBT, youths with depression living with HIV, particularly those in resource-constrained settings such as Uganda, are challenged by numerous barriers to treatment including lack of access to health care and a severe shortage of trained providers [43-45]. As such, there is a need for interventions developed to take into account these numerous treatment barriers and to structure intervention components and delivery methods to fill the gaps in the current system of traditional assessment and treatment access.

A mobile health (mHealth) intervention is a feasible approach for the delivery of interventions to youths with depression living with HIV in Uganda. Upwards of 85% of countries in SSA have accomplished a high level of mobile phone penetration [46]. According to the 2021 Uganda Communications Commission Report, over 70% of Ugandans own a mobile phone [47]. Indeed, several studies in Uganda have used mobile technology to deliver health interventions, including the promotion of correct HIV or AIDS knowledge and testing [48], improving patient-provider communication [49], increasing clinic attendance among individuals on ART [50], and improving HIV care [51].

However, none have focused on addressing depression among youths living with HIV. Moreover, in our own work in Uganda, 80% of youth indicate access to a mobile phone [52]. In neighboring Kenya, a mobile app tested to deliver individual counseling services and facilitate peer support among youth living with HIV documented positive experiences, peer network development, as well as benefits related to treatment adherence, stigma reduction, and mental and behavioral health [53]. Thus, given the many barriers to care experienced by Ugandan youths living with HIV, as well as the lack of access to trained providers [54,55], the proposed Suubi-Mhealth intervention is a viable and sustainable approach for treating depression treatment in this priority population.

This Suubi-Mhealth study will develop a mHealth intervention for use among Ugandan youth with comorbid HIV and depression, taking into account their unique contextual, cultural, and developmental needs. This mobile app will apply user-centered design methodologies we have used to develop and evaluate similar evidence-based digital therapies [56]. The study will be conducted in 2 phases and will be guided by the following specific aims:

Phase 1, aim 1: develop and iteratively refine an intervention protocol for Suubi-Mhealth based on formative work to understand the needs of youths with depression living with HIV (14-17 years).Phase 1, aim 2: based on the results of aim 1, we will explore the feasibility and acceptability of Suubi-Mhealth for use with youths with depression living with HIV on a small scale to inform subsequent refinement for the larger phase of this project.Phase 2, aim 1: pilot-test the preliminary impact of Suubi-Mhealth versus a waitlist control group, on reducing depression (primary outcome) and improving ART adherence, mental health functioning, quality of life, and lowering HIV stigma (secondary outcomes).Phase 2, aim 2: qualitatively examine barriers and facilitators for integrating Suubi-Mhealth into health care settings.

### Theoretical Frameworks Guiding the Study

The Suubi-Mhealth study is guided by two complementary frameworks: (1) the mHealth development and evaluation framework [57], and (2) PRISM (Practical, Robust Implementation, and Sustainability Model) [58]. The mHealth development and evaluation framework involves an iterative process for refining a mHealth intervention through integrating various information sources including published evidence, theory, and formative research with the target group [57]. Specifically, this process involves the following steps: (1) formative research to inform the development of the intervention content and regimen; (2) pretesting to determine the acceptability of the proposed intervention, improve and refine the intervention based on feedback; (3) pilot study to test intervention content and regimen as well as the process, including recruitment and data collection; (4) randomized control trial to test the effect of the intervention in comparison with a control group; (5) qualitative research to improve the intervention and implementation issues and methods; and (6) evaluation and implementation to determine the effect of the intervention once scaled up [57].

Similarly, PRISM is a comprehensive intervention development and implementation framework [58]. It emphasizes the following: (1) organizational perspectives on an intervention (eg, feasibility, adaptability, and barriers); (2) external environment (eg, community resources); (3) recipients’ characteristics (youths, provider, and parent response); and (4) implementation and sustainability infrastructure (training and supervision supports). PRISM provides a framework to study the interaction of interventions with the characteristics of multilevel contexts or factors that may influence uptake, implementation, integration, and youths’ outcomes (youths’ responses, provider preparedness, motivation and fidelity, and community-level support).

## Methods

### Study Overview

The overall goal of this study is to develop a mHealth intervention (Suubi-Mhealth) for use among Ugandan youths with comorbid HIV and depression, taking into account their unique contextual, cultural, and developmental needs. In phase 1 of the study, we will conduct 4 focus group discussions, each with 6-8 youths and 2 focus group discussions with health care providers, for feedback on the proposed intervention content and methods. Based on the results from focus group discussions, we will recruit 30 youths to engage with the Suubi-Mhealth app to explore its feasibility and acceptability so as to inform subsequent refinement for the larger phase of this project. In phase 2, a total of 200 youth from 10 health clinics will be recruited, and randomly assigned to either the Suubi-Mhealth condition or waitlist control condition (5 clinics with 100 youths per condition), to pilot-test the preliminary impact of the intervention on reducing depression and improving ART adherence, mental health functioning, quality of life, and lowering HIV stigma. Upon intervention condition, we will qualitatively examine participants’ intervention experiences, as well as barriers and facilitators for integrating Suubi-Mhealth into health care settings. The hypothesized relationships are provided in Figure 1 below.

**Figure 1 figure1:**
[figure not shown]
Suubi-Mhealth conceptual model. ART: antiretroviral therapy.

### Research Setting

The Suubi-Mhealth study will be implemented in the greater Masaka region located in Southern Uganda, with one of the highest HIV prevalence in the country [4]. Youths will be recruited from health clinics where the International Center for Child Health and Development (ICHAD), which will house the study, and our collaborating institution, Reach the Youth Uganda, operate. For phase 1, youths will be selected from 2 clinics within 1 district. These clinics will be excluded from phase 2. For phase 2, we will select 10 clinics based on size (total number of youth served) and health facility level (levels II, III, IV, or hospital) in each district. For a health clinic to be included in the study, it will have to be credited by the Uganda Ministry of Health to provide ART and have adolescent-friendly services, for example, adolescent clinic days. The procedures have been used in our other studies implemented in the study region [52,59,60].

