### Description of the Study Conditions

In phase 2 of the study, participants will be randomized to 2 conditions (100 youths per condition): a waitlist control condition or the Suubi-Mhealth condition, as detailed below.

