##### Mixed-Effect Models

The principal strategy to examine primary and secondary outcomes over time between the Suubi-Mhealth group and the control group will be the use of linear mixed models and generalized linear mixed models, including a random intercept to allow for the correlation of within-participant measurements over time. Models will include the fixed effects of the intervention group (Suubi-Mhealth vs control), time, and group-by-time interaction. Effect sizes and 95% CIs will be reported.

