##### Sample Size and Power

The primary outcome in aim 1 is whether depression decreases between baseline and postintervention initiation. This is calculated from the depression score change between these 2 time points and categorized as yes versus no. The intracluster correlation for clinics is assumed to be 0.093 and the rate of depression decrease in the control group is 5% [95]. Given our total sample (N=200, 100 youths per condition, 5 clinics per condition), we expect to achieve at least 80% power to detect a rate difference of depression decrease when the rate of depression decrease in the intervention group is 40% and the 2-sided significance level of the test is .05.

##### Milestone for Phase 2, Aim 1

Successful completion of a parallel-group RCT to test the feasibility, acceptability, and preliminary efficacy of Suubi-Mhealth*.* Participants will not experience any adverse events. Participants will have engaged with Suubi-Mhealth daily for 2 months and engaged with at least 75% or more of the modules.

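### Phase 2 describes no restriction on clinic size, facility level or district when ten clinics are split 5:5, and its model carries none of these factors

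*Protocol article*

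**What the plan says.** **Selection.** The Research Setting section says "we will select 10 clinics based on size (total number of youth served) and health facility level (levels II, III, IV, or hospital". This selection is made district by district. The section also requires every clinic to be accredited for ART and to offer adolescent-friendly services.

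**Allocation.** The Study Overview has youths "randomly assigned to either the Suubi-Mhealth condition or waitlist control condition (5 clinics with 100 youths per condition". Description of the Study Conditions says "participants will be randomized to 2 conditions (100 youths per condition". The waitlist section and the Phase 2, Aim 1 overview also speak only of random assignment. Five clinics per condition implies that whole clinics are allocated, and I read it that way. No section says whether the draw is simple, stratified, matched or constrained.

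**Model.** Under Mixed-Effect Models, "Models will include the fixed effects of the intervention group (Suubi-Mhealth vs control), time, and group-by-time interaction". The only random effect named is for the participant: "including a random intercept to allow for the correlation of within-participant measurements over time". Clinic, size, level and district are all absent.

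**Power.** Sample Size and Power states: "The intracluster correlation for clinics is assumed to be 0.093 and the rate of depression decrease in the control group is 5" (per cent). The plan therefore expects outcomes to differ between clinics.

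**The concern.** Size, level and district are known before allocation, and the investigators consider them important enough to choose clinics by. Ten clinics are too few for an unrestricted draw to balance such factors reliably. If facility level is related to how depression changes over time (through counselling, staffing or case mix, say), an uneven split shifts the estimated effect. A later analysis of ten clinics has little room to correct this, and the allocation cannot be redone.

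The described model makes it worse. With no clinic-level error term, the standard error does not include the variation between clinics, so a chance difference between clinics can be read as an effect of the app.

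**Working it through.** **Inputs.** From the article: 10 clinics, 5 per arm, 100 youths per arm (20 per clinic if equal), ICC 0.093, rates of 5% and 40%, two-sided 0.05. Not in the article: the number of clinics at each level, and how much clinic variance size and level explain. Both are treated as assumptions.

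**1. The plan's own power figure.**
- Design effect = 1 + (20 − 1) × 0.093 = 2.767, so the effective sample is 100/2.767 = 36.1 per arm.
- Power for 5% versus 40% is 96% (pooled z) or 93% (unpooled t, 10 − 2 = 8 df). The stated minimum of 80% is reproduced as a lower bound.
- Spending clinic-level degrees of freedom on covariates leaves 92% at 7 df and 90% at 6 df, so adjustment is compatible with the plan's power.

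**2. Chance that a whole level falls in one arm.** There are C(10,5) = 252 splits. For a level with c clinics the probability is 2 × C(10 − c, 5 − c)/252.

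| Clinics at the level | Splits | Probability |
|---|---|---|
| 2 | 112/252 | 44.4% |
| 3 | 42/252 | 16.7% |
| 4 | 12/252 | 4.8% |
| 5 | 2/252 | 0.8% |

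The chance that this happens to at least one level depends on the assumed mix: 0.8% for 5/5, 4.8% for 4/6, 29% for 3/4/3 and 81% for 2/4/2/2.

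**3. Weight of clinic variation.** For an arm difference at a single time point, in outcome SD units:
- Variance = 2 × (0.093/5 + 0.907/100) = 2 × (0.0186 + 0.00907) = 0.0553, so SE = 0.235.
- Clinic share = 0.0186/0.02767 = 67%.
- The clinic component alone has SD √(2 × 0.093/5) = 0.19, a 95% range of about ±0.38 SD.

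**4. What the model leaves uncovered.** For one outcome with this ICC, a between-arm test that ignores clinic has an effective critical value of 1.96/√2.767 = 1.18. Its type I error is about 24% instead of 5%. This applies to an outcome that carries the assumed ICC, such as the change-based yes/no outcome in Sample Size and Power.

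**5. Why main effects are not enough.** In the linear mixed model the treatment effect is the group-by-time contrast, a comparison of changes from baseline. A term for level or size that is constant over time contributes equally at baseline and follow-up, so it cancels. With complete data the estimate and its SE are unchanged. Only factor-by-time terms, or covariates in an analysis of change, act on the contrast.

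**6. Likely gain.** Suppose size and level explain 30% or 50% of clinic variance (assumed).
- 30%: 2 × (0.01302 + 0.00907) = 0.0442, SE 0.210. 50%: 2 × (0.0093 + 0.00907) = 0.0367, SE 0.192.
- That is 20% or 34% less variance, but two covariates take the df from 8 to 6 and the t quantile from 2.306 to 2.447.
- CI half-width: 0.235 × 2.306 = 0.542 before; 0.210 × 2.447 = 0.514 or 0.192 × 2.447 = 0.470 after. With unrounded SEs, it is 5.2% or 13.5% narrower.
- Break-even: 1 − (2.306/2.447)² = 0.112, and 0.112/0.67 = 0.17. If the two covariates explain less than about 17% of clinic variance, adjusting for them widens the interval.

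**7. Feasibility.** With levels at 3/4/3, 6 × (3 × 3 + 3 × 3) = 108 splits are as balanced as possible on level. With 4/6 it is C(4,2) × C(6,3) = 6 × 20 = 120. Either leaves room for a further condition on size.

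**The case against.** **Silence is not a simple draw.** A reader might infer that the plan selects on these factors and then discards them. The article does not support that: it neither states nor excludes restricted allocation, a journal article commonly leaves the method to the full protocol, and the Research Setting section refers its procedures to other studies. Only 'not described' can be said. The model is different, because its terms are written out and omit every one of these factors.

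**The clinics may be similar.** It is tempting to say they were chosen for their spread. Selecting on size and level could equally mean choosing comparable clinics, and the accreditation and adolescent-service requirements narrow the differences. This objection stands. Without counts per level, the chance of separation cannot be narrowed beyond the range from under 1% to about 81%.

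**Chance imbalance is not bias.** Under random allocation the shifts average to zero and are already part of the variation that the ICC describes; a clinic-level error term would cover them. That is right, so the missing clinic term is the firmer defect. Restriction improves precision and comparability but does not replace that term.

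**Baseline differences drop out.** The group-by-time contrast removes stable differences between clinics. Differences in change remain, and the plan attaches its ICC to a change-based outcome.

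**It is a pilot.** Preliminary impact is a modest aim. However, ten clinics are where restriction helps most, and it costs almost nothing.

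**Conclusion.** The point holds as a design improvement worth making before clinics are allocated. The article selects on size, level and district and assumes clinic variation for power, yet describes no restriction on these factors in the draw and carries none of them in its stated model. The chance of separating a level is 44%, 17%, 5% or under 1% for two, three, four or five clinics at that level. Clinic variation makes up about 67% of the variance of a single-time arm difference, at ICC 0.093 and 20 youths per clinic.

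Three limits apply. The counts per level are unknown. The imbalance is a matter of chance. The precision gain from adjustment depends on an explained share that the article does not give, and could be nil or negative if that share is small. All of this assumes that whole clinics are the units allocated; if youths were randomised within clinics, the point would fall away.

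**What to change.** **Allocation (Study Overview and Research Setting).** State that clinics are the units allocated and use restricted randomisation. One workable form lists all 252 splits and keeps those balanced on facility level (hospital or IV versus II or III), clinic size and, where feasible, district. One split is then drawn at random. Keep enough acceptable splits, for example 50 or more, that the draw remains random. If the full protocol already restricts allocation, say so and name the factors.

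**Analysis (Mixed-Effect Models).** Carry the balancing factors as factor-by-time terms, or as covariates in the change-based yes/no analysis described under Sample Size and Power. Add a clinic-level error term alongside them, with degrees of freedom based on the ten clinics. Adding level and size as main effects alone would leave the group-by-time estimate unchanged.

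**Cost.** A short allocation program, a few lines of protocol text, and one or two of the eight clinic-level degrees of freedom. At the stated effect, power stays at 90-92%. Because adjustment for two factors that explain little would widen the interval, fix their number and coding in advance and keep them few.
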